### Combined condition

Heckhausen and Gollwitzer’s [74] action-phase model places the predecisional (i.e., motivational) as preceding a behavioural decision, from which an individual passes through to the preactional (i.e., volitional) phase. Accordingly, participants in the combined condition will first receive the autonomy support component, followed by the implementation intention component. A conceptual map of the intervention components relative to the components in the action-phase model is included in Fig. 2.

### Measures

#### Theory of planned behaviour

Attitude, subjective norm, and perceived behavioural control items will be used based on previous research [38, 91]. *Attitude* will be measured with a common item stem (i.e., “*reducing alcohol consumption during pre-drinking sessions would be*…”) followed by a series of five bipolar adjectives (e.g., *bad-good, beneficial-harmful*), with participants asked to score each adjective accordingly on a six-point scale*. Subjective norm* will be measured with three statements referring to perceived pressure from others to engage in pre-drinking (e.g., “*people who are important to me would want me to reduce my alcohol consumption during pre-drinking sessions”)* with participants asked to respond to each on six-point Likert-type scales ranging from 1 (*strongly disagree*) to 6 (*strongly agree*). *Perceived behavioural control* will be measured with three statements regarding control (e.g., *If I wanted to, I could reduce my alcohol consumption during pre-drinking sessions*), with participants asked to respond to each on six-point Likert-type scales ranging from 1 (*strongly disagree*) to 6 (*strongly agree*). *Intention* to reduce pre-drinking alcohol consumption will be measured with three items (e.g., *I will reduce my alcohol consumption during pre-drinking sessions*) with six-point Likert-type scales ranging from 1 (*strongly disagree*) to 6 (*strongly agree*).

#### Planning

Nine items from the planning subscale of the Self-Regulation Questionnaire [92] will be used to measure participants’ planning ability. Participants will respond to these items (e.g., “*I have trouble making plans to help me reach my goals*”) on six-point Likert-type scales ranging from 1 (strongly disagree) to 6 (strongly agree).

#### Autonomous motivation and goal self-concordance

Sheldon and Kasser [77] have developed a measure of goal self-determination, whereby participants rate how much they pursue goals for specific controlled, non-self-determined reasons (e.g., “…*because somebody wants me to, or because I’ll get something from somebody if I do*”, “*I probably wouldn’t do this if I didn’t get some kind of reward, praise, or approval for it*”), or autonomous, or self-determined reasons (e.g., *because I really believe that it is an important goal to have – I endorse it freely and value it wholeheartedly*). Participants will respond on nine-point Likert-type scales ranging from 1 (*not at all for this reason*) to 9 (*completely because of this reason*). Controlled scores are subtracted from autonomous scores to derive a relative score for goal self-concordance [76].

#### Goal progress

Participants will be asked to rate the extent of their progress, if any, in reducing their alcohol consumption during pre-drinking sessions, on a nine-point Likert-type scale ranging from 1 (*none at all*) to 9 (*total progress*), as used in previous research [78].

#### Pre-drinking alcohol consumption

Participants will report their pre-drinking alcohol consumption in terms of Australian standard drink equivalents consumed during pre-drinking sessions each week, over the previous four weeks, with the aid of a pictorial guide [1], at both baseline and follow-up. The pictorial guide comprises examples of typically served or available portion sizes of alcoholic beverages (e.g., a carton of beer, a bottle of wine or spirits) to aid in participant estimation of pre-drinking alcohol consumption (i.e., pre-purchased quantities such as bottles of spirits or cartons of beer). This approach has been used in previous research [91].

#### Alcohol-related harm

The Brief Young Adult Alcohol Consequences Scale (B-YAACQ) [93] is a validated measure of the experience of alcohol-related harm that is well-suited to use in college populations for the purpose of evaluating change in alcohol consequences. The measure comprises a series of 24 participant-endorsed yes/no statements related to alcohol-related harm (e.g., “*I have felt very sick to my stomach or thrown up after drinking”*). Scores are derived from summing all *yes* responses to create a unidimensional index of alcohol-related harm [93]. Participants will complete the B-YAACQ at baseline and follow-up, to ascertain the effects of the intervention in reducing alcohol-related harm attributable to reductions in pre-drinking alcohol consumption. The time-frame of the B-YAACQ will be modified to refer to harm from alcohol consumption in the previous four-week period, to give a fine-grained view of the effects of the intervention on alcohol-related harm (see [94]).

### Hypotheses

It is hypothesized that participants receiving both autonomy support and implementation intention components will exhibit greater reductions in pre-drinking alcohol consumption and alcohol-related harm at follow-up, relative to participants receiving either intervention component in isolation, in accordance with evidence supporting the combination of these approaches in potentially targeting two important components of the action-phase model [64, 75, 76].

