**Analyses:**

The main and interactive effects of the intervention components in reducing our primary dependent variables, namely, pre-drinking alcohol consumption and alcohol-related harm at four-week follow-up will be tested. Baseline alcohol consumption and demographic information will be included in the analysis as covariates.

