### The present study

The purpose of the present study is to test an online, theory-based intervention to reduce pre-drinking alcohol consumption among undergraduate students who pre-drink. The intervention will test the effects of two theory-based techniques targeting the predecisional and implemental phases of the model of action phases through: (1) facilitating autonomous motivation to reduce pre-drinking alcohol consumption, and (2) prompting the individual to form context-specific implementation intentions to help bridge the goal intention-behavior gap. Combining these techniques should see greater reductions in pre-drinking alcohol consumption and alcohol-related harm than either approach in isolation. The current research makes an original contribution to knowledge by adopting a factorial design, which permits us to examine the independent and interactive effects of two intervention components related to different processes in the model of action phases. The research builds on previous approaches to promoting autonomous motivation [79] and based on current ‘best practice’ recommendations for using implementation intentions [57]. It also follows on from research that suggests that incorporating both motivational and implemental phases is optimally effective in changing health behaviour by targeting multiple processes [38, 80, 81].

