### Participants

Eligible participants will be current undergraduate students who regularly consume alcohol (i.e., are current ‘drinkers’), and have engaged in pre-drinking behaviour within the previous six months. Based on medium effects for implementation intentions on reductions in alcohol consumption reported in Hagger, Lonsdale [33] and the meta-analysis of self-determination theory applied to health contexts reported in Ng et al. [62], we conducted a statistical power analysis using G*Power to ascertain an adequate sample size for the intervention. Specifically, the power analysis was for an Analysis of Covariance (ANCOVA) on the two key dependent variables, alcohol consumption and summed B-YAACQ scores, with the intervention groups as the independent variables powered to detect a medium effect size (Cohen’s *f* = .25) with power set at .80 and alpha set at .025, and baseline scores on the dependent variable as a covariate. The analysis yielded 196 participants (i.e., 49 per group) for each analysis.

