#### Effects of the intervention on pre-drinking alcohol consumption and alcohol-related harm

Two ANCOVAs (autonomy support: present or absent) x 2 (implementation intention: present or absent) will be conducted to ascertain the effect of the intervention on follow-up self-reported pre-drinking alcohol consumption, and summed B-YAACQ scores, at follow-up, controlling for baseline pre-drinking alcohol consumption.

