## Discussion

Pre-drinking is associated with significant risks attributable to excessive alcohol consumption [19, 20, 95]. No theory-based interventions to reduce pre-drinking alcohol consumption have yet to be developed. The present protocol has outlined a theory-based intervention that will attempt to reduce pre-drinking alcohol consumption and alcohol-related harm, by targeting the volitional and motivational phases of action, according to the action-phase model outlined by Heckhausen and Gollwitzer [74]. There is evidence that the provision of autonomy support is associated with greater autonomous motivation to engage in behaviour, and that autonomous motivations for reducing alcohol consumption are associated with reductions in alcohol consumption [33, 69]. Although, exhibiting motivation is a necessary but not sufficient condition for behavioural enactment [49, 96]. Forming implementation intentions has been shown to strengthen the link between intention and behaviour, by providing a link between a contextual cue and an intended response [35, 54]. Combining these approaches is based on the premise that promoting goal self-concordance is important in successful goal attainment [78], and is integral to the efficacy of implementation intention approaches [57, 79]. Therefore, an approach that combines the volitional and motivational action phases, providing individuals with autonomy supportive context for behaviour change and the regulatory skills with which to translate this motivational impetus into behaviour, may be more effective in eliciting successful behaviour change. We therefore expect that while participants in the autonomy support and implementation intention conditions will report lower pre-drinking alcohol consumption at follow-up, the combination of these approaches will see the greatest reduction in pre-drinking alcohol consumption. This is because individuals may be autonomously motivated and intend to reduce their pre-drinking alcohol consumption, let may lack the regulatory capacity required to translate this intention into action (i.e., inclined abstainers) [48]. Similarly, the formation of if-then plans to reduce pre-drinking alcohol consumption may not lead to action if the underlying rationale for these plans is not autonomous [79]. Providing autonomy support to facilitate autonomous motivation will form a sound basis for the development of if-then plans, leading to the translation of that motivational basis into successful action and greater reductions pre-drinking alcohol consumption.

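### The hypothesis compares the combined arm with each single-component arm, but the named primary tests are main effects and the interaction, and no rule links the two

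*Protocol article*

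**What the plan says.** The Hypotheses section contains one hypothesis. It expects greater reductions in consumption and harm with both components "relative to participants receiving either intervention component in isolation". The section on the present study repeats it: "Combining these techniques should see greater reductions in pre-drinking alcohol consumption and alcohol-related harm than either approach in isolation".

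The tests are described differently. The abstract promises to test "The main and interactive effects of the intervention components in reducing our primary dependent variables". The present-study section says that a factorial design was chosen, "which permits us to examine the independent and interactive effects of two intervention components". The Analyses section states: "Two ANCOVAs (autonomy support: present or absent) x 2 (implementation intention: present or absent) will be conducted". None of these places mentions a contrast between the combined cell and a single-component cell, or says which pattern of main effects and interaction would count as support for the hypothesis.

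The Discussion adds an expectation for the single components: "We therefore expect that while participants in the autonomy support and implementation intention conditions will report lower pre-drinking alcohol consumption at follow-up", with the combination showing the largest reduction.

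The Participants section sizes the trial for the ANCOVA, "powered to detect a medium effect size (Cohen’s *f* = .25) with power set at .80 and alpha set at .025", and arrives at 196 participants, 49 per group.

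**The concern.** The hypothesis concerns two simple effects: combined minus autonomy support (AS) alone, and combined minus implementation intention (II) alone. A main effect averages over the other factor, so it brings in the control arm. The interaction asks whether the two effects depart from additivity. Neither is the hypothesised comparison.

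The tests and the hypothesis can therefore disagree in both directions. The combination can be better than each component with no interaction at all, and both main effects can be present when the combination adds nothing to one component. Without a rule fixed in advance, the central claim about combining would depend on which result is emphasised after the data are seen.

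**Working it through.** **Inputs.** From the Participants section: 49 per group, 196 in total, alpha .025, f = .25 (a difference of 0.5 SD for a 1-df effect), and one baseline covariate. The article gives no correlation between baseline and outcome, so effects are expressed in covariate-adjusted SD units (SD = 1). Tests are two-sided at .025 with 196 - 4 - 1 = 191 error df.

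**The plan's own figure.** Noncentral F with lambda = f² x N, alpha .025 and power .80 gives N = 155, 188 and 212 for 1, 2 and 3 numerator df. The stated 196 is not reproduced. That is a separate matter, and nothing below depends on it. At N = 196, power is .89 for a 1-df effect and .76 for the 3-df test.

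**Precision of each test at 49 per cell**
- Main effect: SE = √(1/49) = 0.143. For 0.5 SD the ratio is 3.50 and power is .89.
- Combined versus one single-component cell: SE = √(2/49) = 0.202. For 0.5 SD the ratio is 2.47 and power is .59.
- Interaction (difference of differences): SE = √(4/49) = 0.286. For 0.5 SD the ratio is 1.75 and power is .31.

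The two direct contrasts share the combined cell and so are correlated. Simulation gives a probability of about .43 that both succeed when each gain is 0.5 SD.

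**Scenarios** (200,000 simulated trials each; benefits in the order control / AS / II / both)

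| Benefits | Hypothesis | Both main effects significant | Interaction significant | Both main effects, no significant interaction | Both direct contrasts |
|---|---|---|---|---|---|
| 0 / .5 / .5 / 1 (additive) | true | 80% | 2.5% | 78% | 43% |
| 0 / 1 / 1 / 1 (saturated) | false | 80% | 89%, antagonistic | about 8.5% | 0.2% |
| 0 / .5 / .5 / .75 (sub-additive) | true, gain .25 | 42% | 9% | 38% | 6% |
| 0 / 0 / 0 / .5 (combined only) | true | 10% | 31% | 7% | 43% |

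**Arithmetic behind the rows**
- Additive: 1 - .5 - .5 + 0 = 0, so the interaction is rejected only at its alpha.
- Saturated: each main effect is (1 + 1)/2 - (0 + 1)/2 = 0.5, while combined minus single is 1 - 1 = 0. The difference of differences is 1 - 1 - 1 + 0 = -1.
- Sub-additive: each main effect is (.5 + .75)/2 - (0 + .5)/2 = .375, while the gain from adding the second component is .75 - .5 = .25. Reading the main effects as additive overstates that gain.
- Combined only: each main effect is (0 + .5)/2 - 0 = .25, with power .31. The interaction also has power .31, against .59 for each direct contrast.

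**Sensitivity to the covariate.** If the 0.5 is in raw SD units and the baseline correlation is assumed to be 0, .5 or .7, power per contrast at 49 per group is .59, .73 or .89. The number per group for 80% power on each contrast is then 77, 58 or 39.

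**The case against.** Main effects and interaction are meant to be read together, and most of the extreme outcomes soften when they are. In the additive case, two main effects without an interaction is the usual sign of additive benefit. A reader might infer that the trial would report no benefit of combining, but that would require ignoring main effects that are both significant in 80% of trials. In the saturated case, a reader might infer a wrong conclusion in 80% or 89% of trials. The documents do not support that either: the antagonistic interaction appears in 89%, and the pattern without that warning occurs in about 8.5%. The saturated case also needs 1 SD from each component alone, twice the planning effect. At 0 / .5 / .5 / .5 both main effects are significant in 10% of trials, and in 6.5% without a significant interaction.

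Nor are main effects and interaction out of place. The present-study section names independent and interactive effects as the purpose of the design, and the Discussion expects benefit from each component. It would go too far to say that the combined-versus-single comparison is the trial's only aim, or that the ANCOVA cannot answer it: the needed contrasts come from the same model, and a fuller analysis plan might contain them.

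All of that stands. It does not remove the mismatch, because the point rests on what the article states: one comparison as the hypothesis, and other quantities as the tests. Two main effects imply the hypothesis only if the interaction is truly zero or small. With power .31 for a 0.5 SD difference of differences, a non-significant interaction does not show that. The sub-additive case passes as additive in 38% of trials.

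**Conclusion.** The concern holds as a partial misalignment. The named primary tests serve the factorial aims but do not directly test the hypothesis in the Hypotheses section, and no rule connects them. The consequences depend on the true pattern. The interaction is uninformative about the hypothesis when effects are additive (2.5%). Main effects can be positive when the hypothesis is false, though usually with a warning. When only the combination works, the named tests have power .31 each against .59 for each direct contrast. The stated 80% power does not carry over to the hypothesis: for a 0.5 adjusted-SD gain it is about .59 per contrast and .43 for both.

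These figures assume equal cells of 49 at analysis, normal errors, two-sided alpha .025 and effects in adjusted SD units. A strong baseline correlation would raise power for a given raw difference.

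**What to change.** In each ANCOVA, prespecify two 1-df contrasts of adjusted cell means, using the pooled error term: combined versus autonomy support only, and combined versus implementation intention only. Declare the hypothesis supported for an outcome only if both contrasts favour the combined arm at alpha .025. Because both must succeed, no further split of alpha is needed within an outcome. Keep the main effects and the interaction as the tests of the factorial aims, and say so.

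The wording takes a few lines and the model is unchanged. The cost is power, and the Participants section should state it: the 80% does not apply to these contrasts, and at 49 per group a 0.5 adjusted-SD gain has power of about .59 for each and .43 for both. If the sponsor wants 80% power for each contrast at that gain, 77 per group (4 x 77 = 308 in total) is needed without any credit for the covariate, and power for both together would still be below 80%. The choice should be made before outcome data are seen, and preferably before recruitment closes, so that the sample size can still respond to it.

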### Participants

Eligible participants will be current undergraduate students who regularly consume alcohol (i.e., are current ‘drinkers’), and have engaged in pre-drinking behaviour within the previous six months. Based on medium effects for implementation intentions on reductions in alcohol consumption reported in Hagger, Lonsdale [33] and the meta-analysis of self-determination theory applied to health contexts reported in Ng et al. [62], we conducted a statistical power analysis using G*Power to ascertain an adequate sample size for the intervention. Specifically, the power analysis was for an Analysis of Covariance (ANCOVA) on the two key dependent variables, alcohol consumption and summed B-YAACQ scores, with the intervention groups as the independent variables powered to detect a medium effect size (Cohen’s *f* = .25) with power set at .80 and alpha set at .025, and baseline scores on the dependent variable as a covariate. The analysis yielded 196 participants (i.e., 49 per group) for each analysis.

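### The single .80 power figure names no effect and does not carry over to the stated hypothesis: combined versus one component (49 vs 49) has about .59 power at d = .5 in adjusted SD units

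*Protocol article*

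**What the plan says.** The Participants section describes a G*Power calculation for an ANCOVA on each of the two key outcomes, "with the intervention groups as the independent variables", "powered to detect a medium effect size" (f = .25), "with power set at .80 and alpha set at .025", and with "baseline scores on the dependent variable as a covariate". The result is: "The analysis yielded 196 participants (i.e., 49 per group) for each analysis". The numerator degrees of freedom, the sidedness and the correlation between baseline and follow-up are not given.

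The Hypotheses section contains one hypothesis. Participants who get both components "will exhibit greater reductions in pre-drinking alcohol consumption and alcohol-related harm at follow-up", "relative to participants receiving either intervention component in isolation". The section on the present study says the same: "Combining these techniques should see greater reductions in pre-drinking alcohol consumption and alcohol-related harm than either approach in isolation".

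The analysis section on consumption and harm plans a 2 x 2 ANCOVA for each outcome, and the Abstract says that main and interactive effects will be tested. Neither plans a contrast of the combined arm with a single-component arm.

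**The concern.** The hypothesis compares arms: combined against autonomy support alone, and combined against implementation intention alone, 49 against 49 each time. A 1-df main effect in the same design compares margins of 98 with 98, and an interaction is a difference of differences across all four cells. At one sample size these three tests have very different power. The protocol gives one figure and does not say which test it belongs to.

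The stake is interpretation. Whether to combine the components is the question the trial sets itself. If a contrast or the interaction is not significant, a reader with only the .80 to go on may take that as good evidence against combining. On the protocol's own effect-size scale, the contrast could well have been missed.

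**Working it through.** **Inputs from the protocol.** f = .25, alpha = .025, power = .80, N = 196 in four groups of 49, one covariate (Participants); combined versus each single component (Hypotheses).

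**Assumptions, because the protocol is silent.** Two-sided tests; 49 per group analysed; d = .5 as the effect for a contrast. The last follows from the protocol's own f: for a 1-df effect d = 2f = .5 in covariate-adjusted (error) SD units, and two additive main effects of that size put the combined arm exactly .5 SD from each single arm.

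**Step 1: the stated figure.** ANCOVA F test with noncentrality f²N = .0625 × 196 = 12.25 and error df 196 − 4 − 1 = 191, alpha .025:

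| Numerator df | Power at N = 196 | N for .80 |
|---|---|---|
| 1 (main effect or interaction) | .89 | 155 |
| 2 | .82 | 188 |
| 3 (four-group test) | .76 | 212 |

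None of these gives 196 at .80, so the tested effect cannot be inferred from the number.

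**Step 2: one contrast, adjusted SD.** Noncentrality = d√(n/2) = .5 × √24.5 = 2.475; two-sided .025 with 191 df. Power is .586 (normal approximation .592), so about .59. The smallest d with .80 power is about .63.

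**Step 3: both contrasts.** They share the combined arm, so their correlation is .5. The bivariate normal probability that both exceed 2.241 is .43 (simulation with t statistics: .425).

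**Step 4: dependence on the SD scale.** If d = .5 is in raw SD units and the baseline correlates r with the outcome, the adjusted d is .5/√(1 − r²):

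| r | Adjusted d | One contrast | Both |
|---|---|---|---|
| 0 | .50 | .59 | .43 |
| .5 | .58 | .72 | .60 |
| .6 | .63 | .80 | .69 |
| .7 | .70 | .89 | .82 |

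One contrast is by noncentral t and both by bivariate normal; t-based values for both are about one point lower.

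**Step 5: interaction.** f equals the difference-in-differences divided by 4. A difference-in-differences of .5 adjusted SD is f = .125, with power .31. Power of .80 needs f of about .222, that is 4 × .222 = 0.89 adjusted SD.

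**Step 6: other readings, without covariate gain (one contrast / both).**
- One-sided .025, or two-sided .05: .69 / .55.
- f = .25 as the spread of four means, only the combined arm differing: d = .58, .72 / .59.
- f = .25 as the spread of four means, additive effects: d = .35, .31 / .16.

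All are below .80.

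**The case against.** **The protocol does not claim .80 for this contrast.** That stands. A reader might infer that the trial is said to have 80% power to show combined better than single, but no sentence says so. The calculation is described for the ANCOVA, and the Discussion puts the primary focus on the overall efficacy of the conditions. What remains is that the stated hypothesis has no power figure of its own, and the one figure given does not transfer to it.

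**The shortfall depends on the SD scale.** This also stands. Baseline and follow-up consumption use the same four-week measure, so a sizeable correlation is plausible, and in raw SD units one contrast reaches .80 at r = .6. A reader might infer that the design simply lacks the power; that is too flat. But no correlation is given, and f = .25 entered in a G*Power ANCOVA is on the adjusted scale. For harm, the analysis section adjusts for baseline consumption and not for baseline harm score, so a correlation suited to repeated consumption reports need not apply there.

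**Requiring both contrasts is a choice.** True. The protocol sets no success rule, and .43 applies only if beating either component means beating each one.

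**Under additive effects the main effects answer the question.** With no interaction, combined versus autonomy support alone estimates the implementation intention main effect, which has power .89. This is coherent, but the protocol does not say that it assumes no interaction. Its section on combining approaches argues for synergy, and the present-study section justifies the factorial design by independent and interactive effects.

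**f = .25 is conventionally medium for any term, including an interaction.** Accepted. The point is only that for the interaction it means a difference-in-differences of 4 × .25 = 1.0 adjusted SD, which should be visible to the reader.

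**Conclusion.** The concern holds in a limited form. The stated .80 is not tied to an effect, is not consistent with N = 196 for 1, 2 or 3 numerator df, and does not carry over to the only formal hypothesis. On the adjusted-SD scale that f = .25 implies for a 1-df effect, with two-sided alpha .025 and 49 analysed per arm, power is about .59 for one contrast and .43 for both. On a raw-SD scale the shortfall narrows as the baseline correlation rises. It closes at about r = .6 for one contrast and about r = .7 for both. Loss below 49 per arm at follow-up would reduce all of these figures.

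The documents do not support going further and calling the sample inadequate: the main effects have .89 power at f = .25, and the correlation that decides the contrasts is unknown. Should-fix.

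**What to change.** 1. In Participants, state which effect was powered and its numerator df, and correct either the N or the power. At f = .25 and alpha .025, the pairs for 196 are .89, .82 or .76, and the N for .80 is 155, 188 or 212, for 1, 2 or 3 df.
2. In the analysis section on consumption and harm, add the contrasts of combined versus each component, estimated from the same 2 x 2 ANCOVA, and say whether one or both must be significant. Alternatively, state that the hypothesis is tested through the two main effects on the assumption of no interaction.
3. Report power by test at N = 196: main effects; the contrasts as a range over the baseline correlation, with a detectable d of about .63 adjusted SD; and the interaction, detectable at a difference-in-differences of about 0.89 adjusted SD (f about .22).
4. State that non-significant contrasts or a non-significant interaction will be interpreted through confidence intervals and not as absence of benefit.

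The cost is text and two added contrasts per outcome. The target of 196 can be kept by correcting the stated power, and randomisation and outcomes are unchanged. The stated power becomes less favourable for the hypothesis.

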### Intervention components

Participants will be randomly allocated to one of four conditions: a control condition, an autonomy support condition, an implementation intention condition, and a combined autonomy support and implementation intention condition. Each condition will include the first two guidelines of the Australian National Health and Medical Research Council safe drinking guidelines [1]. These guidelines are recommendations for keeping alcohol consumption within limits to reduce the risk of alcohol-related harm over the lifetime, and are included in the Appendix. (Fig. 2) shows the intervention components alongside the intended action phase targets. 

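### The stated sample size of 196 does not follow from the stated inputs (f = .25, alpha = .025, power = .80) for any numerator degrees of freedom that a 2 x 2 design allows

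*Protocol article*

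**What the plan says.** The sample size calculation is in the Participants section of the Methods. It names the software ("we conducted a statistical power analysis using G*Power") and the test: "the power analysis was for an Analysis of Covariance (ANCOVA) on the two key dependent variables". The trial is "powered to detect a medium effect size (Cohen’s *f* = .25"), "with power set at .80 and alpha set at .025", with "baseline scores on the dependent variable as a covariate". The result is given as direct output: "The analysis yielded 196 participants (i.e., 49 per group) for each analysis". The numerator degrees of freedom are not stated.

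The design is fixed elsewhere in the article. Under Intervention components: "Participants will be randomly allocated to one of four conditions". The Analyses section plans one two-factor ANCOVA for each of the two primary outcomes, the second factor being "2 (implementation intention: present or absent) will be conducted to ascertain the effect of the intervention". Attrition appears only among the limitations in the Discussion, as something recruitment will try to allow for, so 196 is not presented as a figure inflated for drop-out.

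**The concern.** The paragraph gives effect size, alpha, power, test, software and covariate, and the design fixes the number of groups. Only the numerator df is left open, and a 2 x 2 design permits few values: 1 for each main effect and for the interaction, and at most 3 for all differences among four groups. A reader should therefore reach 196 with one of them, and cannot.

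This is the article's only statement of power. As it stands, nobody can tell which test the trial was sized for, or whether the .80 is attached to the right test. The two natural readings err in opposite directions: for the 1-df factorial effects, 196 is more than the stated power needs; for a joint four-group comparison, it is too few.

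**Working it through.** **Inputs.** From Participants: f = .25, alpha = .025, power = .80, one covariate. From Intervention components and Analyses: 4 groups in a 2 x 2 layout. Numerator df (df1) is not stated, so each candidate is tried.

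**Formula.** For a fixed-effects ANCOVA, G*Power uses the noncentral F distribution with

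- noncentrality λ = f² × N = .0625 × N
- denominator df2 = N − groups − covariates = N − 4 − 1 = N − 5
- power = P(F′(df1, df2, λ) > F critical at alpha)

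The required N is the smallest one with power of at least .80.

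**Attempt to reproduce 196 from the stated inputs (f = .25, alpha = .025).**

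| df1 | What it would test | Required N | λ = .0625 × N | df2 |
|---|---|---|---|---|
| 1 | a main effect, or the interaction | 155 (156 with equal groups) | 9.69 | 150 |
| 2 | no single effect in a 2 x 2 | 188 | 11.75 | 183 |
| 3 | all four groups jointly | 212 (53 per group) | 13.25 | 207 |
| 4 | not available with four groups | 231 | 14.44 | 226 |

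The required N passes from 188 to 212 without touching 196. Rounding up to a multiple of four gives 156, 188, 212 and 232. For 1 to 3 df, raising the number of covariates to 10 leaves 155, 188 and 212 unchanged, so the covariate set is not the explanation. As a cross-check, a two-group comparison of means with d = .5 at two-sided alpha .025 needs 154 in total, in line with 155 for the 1-df F test.

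**Search for what does give 196.** At f = .25 and alpha = .05, the required N is 128 (1 df), 158 (2 df), 179 (3 df) and 196 (4 df). The last is exact: N = 195 gives power .798 and N = 196 gives .8005. Other routes reach 196 by changing f instead: at alpha = .025, f = .26 with 3 df, or f = .245 with 2 df. Enlarging f for a baseline-to-follow-up correlation of about .275 also gives 196 with 3 df. Dividing alpha by three (.025/3) with 1 df comes close, at 198. The article describes none of these.

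**Power at the stated size.** With N = 196, λ = .0625 × 196 = 12.25 and df2 = 191. At alpha = .025:

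- 1 df: .892
- 2 df: .820
- 3 df: .762

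**What f = .25 means for each 1-df effect.** With four equal cells, an effect of f = .25 moves cell means by ±.25 SD.

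- Main effect: the two factor levels differ by .25 + .25 = .5 SD (d = .5).
- Interaction: the cells deviate by +.25, −.25, −.25, +.25, so the difference of differences is (.25 + .25) − (−.25 − .25) = 1.0 SD.

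The .89 therefore refers to a half-SD main effect, or to an interaction contrast of a full SD.

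**The case against.** The best defence is that the error is harmless. The Analyses section plans 2 x 2 ANCOVAs, whose effects have 1 df each. For those, 196 analysed gives power .89 at alpha .025, and the stated .80 errs on the cautious side. Only the 3-df test falls short, and no section names an omnibus four-group test as the planned analysis. This stands. It settles how much the error matters, but it does not make 196 the output of the stated inputs.

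Three stronger readings are tempting, and the article does not support them.

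- *The trial is too small.* A reader might infer this from the .76. It is conditional on the 3-df test being the one meant. The Participants section calls the intervention groups the independent variables, which is ambiguous, while the Analyses section points to the factorial effects.
- *The calculation ignored the two-outcome alpha of .025.* This rests wholly on the back-solved match at alpha = .05. The article says .025 and shows no software output. Entering the number of groups as the numerator df is a plausible slip, but it is conjecture.
- *196 arises only from alpha = .05 with 4 df.* The routes through f = .26 or f = .245 show otherwise. That combination is only the exact match at f = .25 among conventional alpha levels.

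**Conclusion.** The stated figure is wrong for its own inputs. At f = .25, alpha = .025 and power .80, the required N is 155 for a 1-df effect, 188 for 2 df and 212 for 3 df. Against 196, that is 196 − 155 = 41 more than needed for the factorial effects, or 212 − 196 = 16 fewer than needed for the joint test. The cause cannot be established from the article.

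The conclusion assumes G*Power's standard ANCOVA routine with f entered as stated, equal groups, and 196 as the number analysed. It does not depend on any view of how the slip arose. The planned 1-df tests are adequately powered at f = .25, so what needs correcting is the sample-size justification. The size of the trial can stay as it is.

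**What to change.** Keep 196 analysed participants. In the Participants section, state the numerator df and the alpha actually used, and replace the power statement with one that can be reproduced, for example:

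*With 49 participants analysed per group, alpha = .025 and one covariate, power is .89 for each 1-df effect of f = .25. For a main effect this is a difference of .5 SD between factor levels; for the interaction it is a difference of differences of 1.0 SD.*

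Both translations of f should be given, because quoting d = .5 alone would suggest .89 power for a half-SD interaction, which is not what was calculated.

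If the 3-df four-group test was meant, say so and report its power as .76, noting that .80 would need 212 (53 per group).

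The cost is the wording of one paragraph. For the factorial tests as planned, design, alpha, analysis and recruitment are unchanged.
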